### **5. TREATMENT OF SUBJECTS:**

Those schoolchildren who fulfilled inclusion criteria will be recruited for the trial. A total of 236 schoolchildren (see sample size calculation on section 10.2) with *S. mansoni* who fulfilled the inclusion/exclusion criteria would be randomly assigned to two groups of 118 each. One group will be given a single dose of PZQ 40 mg/kg and the other a single dose of PZQ 60mg/kg body weight. Table 2 below illustrates the treatment groups.

Table 2. Study groups for and *S. mansoni* treatment.

| Dosage of PZQ/kg body weight | S. mansoni subjects (N) |
|------------------------------|--------------------------------|
| 40 (single dose) – Control   | 118                            |
| 60 (single dose)             | 118                            |

Praziquantel is provided in tablets of 600mg with 3 scores, which may be divided in 4 segments of 150 mg each. The amount of drug to be given can be adjusted to the patient's bodyweight by breaking the tablets in 4 segments. A reference table for the number of tablets to be given for each participant according to treatment regimen and body weight is presented in Appendix 2.

#### 5.1. Compliance to treatment:

The medication will be given and directly observed by the person designated to provide treatment. If the participant vomits within 30 minutes after taking the medication, a new dose will be given.

#### 5.2. Medications permitted and not permitted:

All medications except those with anti-schistosomal activity will be allowed during the trial. After the 21 days safety assessment, participants with diagnosis of intestinal helminths will be treated with mebendazole or albendazole. Those with anemia (as defined in section 6.2.4) will receive iron supplementation. If the participant has severe anemia he/she will be referred to appropriate health care.

#### 5.3. Accountability of the investigational product (PZO):

The PZQ for this trial will be received by the Principal Investigator and stored at room temperature (temperatures between 18°C and 24°C) in the Institute's drug store. The PI will keep a register of drugs received, dispensed and returned from the field.

## **6. CLINICAL AND LABORATORY PROCEDURES**

### 6.1. Clinical examination:

#### 6.1.1. Clinical malaria

Signs and Symptoms of clinical malaria will be determined (by one of the study physicians) on schoolchildren recruited in the study after satisfying inclusion criteria before treatment with PZQ. Those with fever (temperature  $\geq 37^{\circ}\text{C}$ ) and/or showing one or more of the following signs and symptoms, i.e., body malaise, headache, vomiting or diarrhoea will be considered to have clinical malaria will referred for treatment at a nearby clinic and excluded from the study.

### 6.2. Laboratory examination

#### 6.2.1. Pregnancy

Eligible female on childbearing age satisfying inclusion/exclusion criteria, after giving informed consent, will be examined for pregnancy using the Quickstick™ One step HCG Pregnancy Test. Each participant will provide a fresh urine specimen and tested within 24 hr of sample collection. The test device (dipstick) is dipped in the urine sample and results are read in 5 minutes. The presence of two colour bands (pink to purple) within the test region of the device indicates a positive result. The test is, however, sensitive 7 days after a female has conceived. Each participant with positive pregnancy test will be counselled by one of the study nurses.

#### 6.2.2. Stool:

At baseline and during follow-up visits each child in schools within 5 km of the Lake Victoria shore recruited in the study will provide a stool specimen on two separate days at maximum interval of 5 days. Duplicate Kato Katz slides (2 slides) (Katz et al., 1972) will be prepared in the field (using the 41.7mg faecal template) from each stool sample. The prepared Kato slides in the field will undergo quantitative microscopic examination for *S mansoni* ova.

Classification as egg count  $\geq 100$  eggs per gram of faeces for *S mansoni* will be obtained by the mean egg count for the 4 slides collected at baseline.

#### 6.2.3. Urine

At baseline, as outlined in Table 1, each child in schools recruited in the study will provide one urine specimen between 10am and 2pm. The urine sample will be semi-quantitatively examined for *S haematobium* infection by reagent strips (Hemastix® Bayer) reading for microhaematuria.

Participants positive for *S. haematobium* will be excluded from the study, but treated with the standard regimen of PZQ 40mg/Kg.

#### 6.2.4. Blood

Finger prick blood will be obtained in a Hemocue cuvette from each school child at baseline and follow-up visits D21, Month 6 and Month 12 and examined for haemoglobin level (Hb) by a digital hemoglobinometer (Hemocue). Hb reading of  $\leq 11$ g/L will be considered as anaemia and that of  $\leq 7$ g/L as severe anaemia.

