In Tanzania PZQ at 40mg/kg body weight as a single dose has been tested against infections by *S haematobium* (McMahon & Kolstrup, 1979) and *S mansoni* (Rugemalila et al., 1984). McMahon & Kolstrup (1979) recorded high cure rates of 83%, 76% and 71% against *S haematobium* at 1- month, 2- months and 6- months, respectively. In *S mansoni*, however, Rugemalila et al. (1984) observed lower cure rates of 35%, 56% and 63% at 1-month, 2- months and 6- months, respectively.

The unusually low cure rates reported by Stelma et al. (1995) in Senegal, while working in very intense focus of *S. mansoni*, has raised much concern about the emergency of resistance or tolerance of schistosomes to PZQ. So in order to circumvent this problem, several strategies to reduce the rate of schistosome species developing resistance against PZQ and to optimize the use of PZQ in schistosomiasis control has been suggested. In the present study, the suggested option to be explored is to increase the dose regimens of PZQ up to 60mg/kg body weight.

Stelma et al. (1997) increased the dose of PZQ from standard dosage of 40mg/kg to 60mg/kg and showed to have no significant improvement in efficacy. Van Lieshutt et al. (1994), however, showed that the opposite was true. This controversy requires to be urgently resolved by collecting data on the safety, efficacy and effectiveness of increased doses of PZQ in different epidemiological setting where schistosomiasis is highly endemic.

Children are especially vulnerable to schistosomiasis, and infected school-age children are often physically and intellectually compromised by concurrent anemia, attention deficits, learning disabilities, school absenteeism and higher dropout rates (Guyatt et al., 2001; WHO, 2002). Schistosomiasis Control Programs target school-aged children, aiming for clinical cure and morbidity reduction. Many previous trials were done with children and adolescents to test the efficacy of praziquantel alone or in combination with other drugs (Jaoko et al., 1996; Guisse et al., 1997; Olds et al., 1999; Urtzinger et al., 2000; de Clercq et al., 2002). Since praziquantel is a safe and well known drug (as described above) and the improvement of treatment should be achieved for those who need the most, children and adolescents will be the chosen study population for this trial.

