#### D0 (means 7 days after baseline study +/-1 day)

Clinical history of each schoolchild fulfilling screening criteria using questionnaire will be taken to see if the subject has acute or chronic severe disease, including hepato-splenic schistosomiasis. In addition, the questionnaire will seek to establish a history of adverse reactions associated with PZQ, a history of treatment with PZQ within 30 days and medication (such as antibiotics) currently being used which may affect the results of the present trial. This will be followed by a thorough physical examination by a physician for physical fitness to participate in the trial. Those showing signs and symptoms of clinical malaria will be referred for treatment and excluded from the study and referred for treatment. Childbearing age female subjects will further be tested for pregnancy using the Quickstick™ One step HCG Pregnancy Test. Those tested positive for pregnancy will be excluded from the study. Each girl will be given individual counseling from the study nurse. Those children with schistosomiasis who will be excluded from the study at this point will be treated with a single oral dose of PZQ at 40mg/kg.

For the children who fulfill all criteria for enrolment, body weight will be determined and a finger-prick blood sample will be collected for Hb measurement. Thereafter they will be treated with PZQ according to weight and dosage regimen assigned in the trial (see randomization and blinding section for treatment assignment). During the 4 hours post-treatment study subjects will be observed for occurrence of adverse events and by the end of this period they will be assessed for adverse events using a questionnaire.

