## **10. DATA PROCESSING AND ANALYSIS**

The data will be double entered into a computer using dBase programme by two different data entry clerks and the entered data will then be verified and cleaned before being subjected to analysis using STATA.

10.1. Analysis of data: Chi- square or Fisher's exact test will be used for comparison of proportions (ex. cure rate & egg reduction rate, frequency of AEs and severity of AEs) and Student's t test for comparison of means (geometric mean egg output, variation of Hb level and weight) in the two treatment groups (PZQ 40mg/kg and 60mg/kg).

10.2. Sample size:

Assuming the cure rate of a standard dosage (40mg) of Praziquantel is 60% and increasing the dosage to 60mg would improve cure rate to *at least* 80%, a sample size of 91 infected schoolchildren per study group will be needed. This sample size will give a study power of 80% at 5% significance level. Considering a drop out of about 30% due to loss to follow-up or medical grounds, 118 study subjects will be needed for each study group making a total of 236 schoolchildren.

10.3. Quality Control:

During laboratory examination of stool and urine specimens, a 10% sample of specimens will be re-examined by an independent technician (one who is not part of the research team) every day and results compared to see the degree of agreement.

10.3.1. For Kato-Katz examinations:

10% of the slides read by each microscopist will be randomly selected and re-examined by an experienced microscopist designated by the PI.

*For cure rate* (agreement between positive/negative slides) the maximum discordance rate acceptable will be 5%. Above 5% all slides will have to be read by the experienced microscopist.

*For infection intensity*, levels of infection will be defined as:

| Number of eggs/slide | Approximate egg count/g of stools |
|----------------------|-----------------------------------|
| 1-4                  | ~ 1-100                           |
| 5-12                 | ~ 100-300                         |
| 13-25                | ~ 300-600                         |
| 26-41                | ~ 600-1.000                       |
| >41                  | ~ 1.000                           |

Disagreement will be defined when the 2 readings result in different levels of infection, according to this classification. The maximum level of disagreement accepted will be 5%.

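### Section 6.2.4 states the anaemia and severe-anaemia cut-offs in g/L where g/dL was probably meant, so the iron and referral rules in section 5.2 could not trigger if applied as written

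*Protocol*

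**What the plan says.** Section 6.2.4 (Blood) has finger-prick blood taken at baseline, day 21, month 6 and month 12 and "examined for haemoglobin level (Hb) by a digital hemoglobinometer (Hemocue"). It does not say in which unit the device displays. It then defines two categories. A reading at or below 11 "g/L will be considered as anaemia and that of" at or below 7 "g/L as severe anaemia". The unit is g/L in both places.

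Section 5.2 acts on these categories: "Those with anemia (as defined in section 6.2.4) will receive iron supplementation". The next sentence adds: "If the participant has severe anemia he/she will be referred to appropriate health care". The iron rule cites 6.2.4 by number. The referral rule does not, but 6.2.4 is the only place where severe anaemia is defined.

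Haemoglobin also appears in the endpoints, the visit descriptions, Table 1 and sections 8.2, 9 and 10.1. None of these gives a unit or a cut-off, so nothing elsewhere corrects 6.2.4.

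**The concern.** The written cut-offs are not physiologically possible in this population. Before treatment, every child has a "thorough physical examination by a physician for physical fitness to participate in the trial", and acute or chronic severe disease is an exclusion. A definition that no participant can meet makes any rule resting on it inoperative.

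The two rules decide who receives iron and who is sent for care. The introduction describes infected school-age children as often "physically and intellectually compromised by concurrent anemia", so they were evidently meant to be used. What is at stake is participant care. The comparison of the two doses does not use the cut-offs.

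**Working it through.** **Inputs**

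- Cut-offs as printed: 11 g/L and 7 g/L (Protocol 6.2.4).
- Participants: 236, or 118 per group (Protocol 5 and 10.2).
- Haemoglobin distribution and anaemia prevalence: not given in the protocol, so both are assumed below.

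**Step 1: conversion.** 1 g/dL = 10 g/L.

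| Category | As printed | Same value in g/dL | Numeral read as g/dL | That value in g/L |
|---|---|---|---|---|
| Anaemia | 11 g/L | 11 / 10 = 1.1 | 11 g/dL | 11 × 10 = 110 |
| Severe anaemia | 7 g/L | 7 / 10 = 0.7 | 7 g/dL | 7 × 10 = 70 |

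The printed values are one tenth of the plausible ones.

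**Step 2: how many children could meet the printed cut-offs.** Assume that Hb is normally distributed with a mean of 100 to 130 g/L and an SD of 10 to 20 g/L. The expected number at or below a cut-off c is 236 × Φ((c − mean) / SD).

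- The case most favourable to the printed cut-offs is mean 100, SD 20.
- For 11 g/L: z = (11 − 100) / 20 = −4.45, giving 0.001 children.
- For 7 g/L: z = (7 − 100) / 20 = −4.65, giving 0.0004 children.
- Every other combination tried gives less, so in practice the number is 0 of 236 for both.

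**Step 3: the same model with the corrected cut-offs.**

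- 110 g/L: from 5 children (mean 130, SD 10, z = −2) to 199 (mean 100, SD 10, z = 1).
- 70 g/L: from effectively 0 (mean 130, SD 10, z = −6) to 16 (mean 100, SD 20, z = −1.5).

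Once the unit is corrected, the anaemia rule works and the severe-anaemia rule can trigger.

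**Step 4: children who would miss iron under a literal reading.** Assume that 10% to 40% have Hb at or below 11 g/dL.

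- 0.10 × 236 = 23.6, about 24.
- 0.40 × 236 = 94.4, about 94.

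**Step 5: which reading occurs in the field.**

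- g/dL display, numerals taken as intended: no child is missed.
- g/L display, printed cut-offs applied: a child at 65 g/L, below the probable intended limit of 70 for severe anaemia, is above both printed limits and gets neither iron nor referral.
- g/dL display, values converted to match the text: the outcome is the same as with a g/L display.

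The protocol does not state the display unit, so the text does not settle which of these happens.

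**Step 6: does the analysis use the cut-offs?** Section 10.1 applies Student's t test for "comparison of means (geometric mean egg output, variation of Hb level and weight"). Hb enters as a continuous change from baseline. The primary endpoint is cure rate at day 21, and the sample size rests on cure rates of 60% and 80%. None of these depends on the cut-offs.

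**The case against.** The strongest reply is that the slip corrects itself. The values are so plainly impossible that a physician would read 11 and 7 as g/dL. On a g/L display every reading would be around ten times the printed limit, which would expose the mistake on the first day. The field team includes at least one physician, and nothing suggests that one would pass a reading of 6 g/dL as normal because of this line. I agree that this is the likelier course. It still relies on staff overriding the written rule, in a trial that section 3 says will be run in compliance with the protocol.

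A second reply is that the headcount says little. This is largely right. It is conditional on literal application and on an assumed prevalence, and the normal model in the working gives a much wider range (5 to 199). The denominator may also be too large. Section 5.2 introduces this care after the day 21 safety assessment, although the iron sentence does not repeat that timing, and 236 includes an allowance for drop-out. On the 182 children the plan needs (2 × 91), the same 10% to 40% gives 0.10 × 182 = 18.2 to 0.40 × 182 = 72.8, about 18 to 73. The firm figure is the factor of ten.

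A third reply is that the trial's conclusions are safe. That also stands. Iron could move Hb at months 6 and 12, but the rule is the same in both randomised groups, so there is no evident bias between doses.

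None of this disputes that the unit as printed is wrong. Because g/L appears in both places, a single stray character is an unlikely explanation.

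**Conclusion.** The concern holds. Section 6.2.4 states both cut-offs in a unit that makes them about ten times too low, and no other part of the protocol corrects it. Applied literally, 0 of 236 children would meet either definition, and neither the iron rule nor the referral rule in section 5.2 would trigger. Under an assumed prevalence of 10% to 40%, about 24 to 94 children would then go without iron. The number who would miss referral cannot be fixed from the document; under the assumed Hb distributions it is 0 to 16. If staff use the numerals as g/dL, which is probable, no child is missed.

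That g/dL was intended is an inference from plausibility, since the protocol does not say so. The reach is limited to participant care. This should be fixed because it is a wrong threshold in an operative care rule, but it does not threaten the efficacy or safety comparison.

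**What to change.** In section 6.2.4, change the cut-offs to ≤ 11 g/dL for anaemia and ≤ 7 g/dL for severe anaemia, or equivalently ≤ 110 and ≤ 70 g/L. The clinical lead should confirm that these are the intended figures. State the same unit for the device reading and for its record, so that the rule and the number it is applied to cannot differ.

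The cost is a one-line correction. Section 5.2 needs no change, and the sample size, visits and analysis are unaffected.

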#### 6.2.5. Weight

Weight of schoolchildren will be measured at baseline, at 6-months and 12 –months post treatment with PZQ. A digital, battery operated, electronic balance (Tanita digital Model THD - 305) will be used to weigh schoolchildren.

### **7. ASSESSMENT OF EFFICACY:**

7.1. Parameter to be measured – egg count, as measured by the Kato-Katz method described above, at baseline, D21, 6M and 12M

The measurement of egg count for each time point will be estimated as the mean of the 4 slides collected (2 slides per sample, 2 samples within 5 days).

#### 7.2. Methods for assessing efficacy:

- Cure rate will be estimated as the proportion of subjects with negative result at 21 days after treatment.
- Egg reduction rate at 21 days after treatment will be estimated through the following formula:  
 $[1 - (\text{epg2} / \text{epg1}) \times 100]$  where epg1 and epg2 are the geometric mean of  $\log_{10}$  transformed (x+1) numbers of eggs per gram of faeces at the screening survey and the 21st day post-treatment survey.

The same calculations of cure rate and egg reduction rate will be estimated for the 6M and 12M follow-up in order to estimate reinfection rates.

7.3. Analysis: The cure rate and egg reduction rate will be compared between the 2 treatment regimens, PZQ 40mg/Kg and 60mg/Kg.

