#### 6M (means 180 days after treatment +/- 7 days)

At 6M follow up cure rate, egg reduction rate, weight and Hb will be determined in all study subjects in the trial. Therefore, stool samples will be collected on two separate days and each day duplicate Kato slides will be made for quantitative examination of *S mansoni* ova. This will allow cure rate and egg reduction rate at 6M to be calculated.

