#### 12M (means 365 days after treatment +/- 14 days)

At this follow up activities conducted at 6M will be repeated, that is, cure rate, egg reduction rate, weight and Hb will be determined in all study subjects in the trial. Therefore, stool samples will be collected on two separate days and each day duplicate Kato slides will be made for quantitative examination of *S. mansoni* ova. This will allow cure rate and egg reduction rate at 12M to be calculated.

Table 1. A summary of study procedures are presented below for each visit:

|                               | Screening | Day 0 | Day1 | Day 21 | Month 6 | Month 12 |
|-------------------------------|-----------|-------|------|--------|---------|----------|
| Clinical history              | X         | X     |      |        |         |          |
| Inclusion/Exclusion criteria* | X         | X     |      |        |         |          |
| Cure rate                     |           |       |      | X      | X       | X        |
| Egg Reduction Rate            |           |       |      | X      | X       | X        |
| Adverse events                |           | X     | X    | X      |         |          |
| Weight                        |           | X     |      |        | X       | X        |
| Hb                            |           | X     |      | X      | X       | X        |

\* Screening for exclusion criteria includes urine test for pregnancy (childbearing age female participants) and diagnosis of *S. haematobium*.

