#### 4.3. Subject withdrawal criteria

The study subject will be withdrawn from the trial if he/she presents any illness or condition that makes further participation impossible, or if he/she decides not to participate. The participant will be discontinued to participate in the study if during the follow-up period he/she takes an anti-schistosomal medication.

Withdrawn participants will not be replaced. Individual children will be free to withdraw from the study for whatever reason they chose.

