## **11. ETHICAL CONSIDERATIONS FOR PROJECTS INVOLVING HUMAN SUBJECTS**

Research clearance for the proposed study has been obtained from the Medical Research Co-ordinating Committee of the National Institute for Medical Research, which acts as the National Ethics Committee in Tanzania and is attached.

At the beginning of the study meetings will be organized with parents and teachers of the earmarked schools, whereby detailed information will be provided by the research team about the aims, procedures, benefits and potential risks of the study.

Written informed consent will be obtained from all participants. In case of minors, the oral assent of the child will be asked, besides the written consent of the guardian. If the children is between 10-<14, and according to the Investigator's perception, he/she is not able to understand the information given during the informed consent procedure, the oral assent is not necessary.

Participation in the study will be on voluntary terms and that an individual will be free to withdraw from the study at any time. Withdrawal from the study will not affect ones statutory rights in any way.

All records of study subjects will be kept confidential.

All schoolchildren participating in the study and found to have schistosomiasis will be treated free of charge. Participants with schistosomiasis who do not fulfil the criteria for enrolment will be treated with the standard regimen of single dose Praziquantel at 40 mg/Kg.

Only parasitological specimens (Kato-Katz slides) will be kept for the duration of the study to allow for quality control and cross-checking. They will then be discarded. No other specimens will be kept.

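### Reinfection at 6 and 12 months is estimated over all children, so day-21 treatment failures are counted as reinfections and a difference in cure can pass for a difference in reinfection

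*Protocol*

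**What the plan says.** Section 7.2 defines cure first: "Cure rate will be estimated as the proportion of subjects with negative result at 21 days after treatment". It defines the egg reduction rate from geometric means of the "numbers of eggs per gram of faeces at the screening survey and the 21 st day post-treatment survey". It then carries both forward: "The same calculations of cure rate and egg reduction rate will be estimated for the 6M and 12M follow-up in order to estimate reinfection rates". Section 7.3 compares cure rate and egg reduction rate between the two regimens.

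The visit descriptions in section 3.2 set the denominator. For 6 months: "At 6M follow up cure rate, egg reduction rate, weight and Hb will be determined in all study subjects in the trial". For 12 months: "cure rate, egg reduction rate, weight and Hb will be determined in all study subjects in the trial". Nothing limits the estimate to children negative at day 21, and nothing moves the reference for egg reduction from screening to day 21.

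Two other passages bear on who is still measured at those visits. Section 4.3 states: "The participant will be discontinued to participate in the study if during the follow-up period he/she takes an anti-schistosomal medication". It adds: "Withdrawn participants will not be replaced". Section 11 states: "All schoolchildren participating in the study and found to have schistosomiasis will be treated free of charge". The protocol does not say whether that last sentence reaches children found positive after enrolment.

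The listed endpoints in section 3.2 are day-21 cure (primary) and, as secondary, day-21 egg reduction, adverse events, haemoglobin change at 21 days, 6 and 12 months, and weight change at 6 and 12 months. Cure and egg reduction at 6 and 12 months are measured but are not listed endpoints.

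**The concern.** Reinfection means a new infection in a child who had been cleared. A proportion positive over all treated children mixes two groups: those never cleared and those cleared and infected again. If one dose cures more children, that arm has fewer persistent positives and will appear to have less reinfection even when exposure and true reinfection are identical. The same holds for egg reduction measured against screening. A reader would take a difference in efficacy, already counted at day 21, for a second and separate benefit.

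The rule in section 4.3 raises a related but lesser question. Taking an anti-schistosomal drug during follow-up is more likely in a child who is still infected. Treatment is a single dose, so discontinuation under this rule stops no trial treatment. It only stops data collection. Haemoglobin and weight at 6 and 12 months are listed secondary endpoints, and the loss would depend on a post-randomisation factor linked to treatment failure.

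**Working it through.** **Inputs**
- Day-21 cure c: 60% at 40 mg/kg, 80% at 60 mg/kg (section 10.2).
- 91 evaluable and 118 randomised children per arm (section 10.2).
- True reinfection r among children cured at day 21: not given. Assumed equal in both arms, range 10% to 30%.
- Share k of day-21 positives who later turn negative: not given. Assumed 0 at first, then varied.

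**The plan's own figure.** For 60% v 80%, two-sided 5%, 80% power:
- uncorrected n = [1.96 × √(2 × 0.7 × 0.3) + 0.842 × √(0.6 × 0.4 + 0.8 × 0.2)]² / 0.2² = 81.2, so 82;
- with continuity correction, (81.2/4) × [1 + √(1 + 4/(81.2 × 0.2))]² = 91.

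The stated 91 reproduces. The protocol gives no figure for reinfection.

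**Share positive at 6 or 12 months over all children, failures staying positive**

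Share positive = (1 − c) + c × r = 1 − c(1 − r)

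| r | 40 mg/kg | 60 mg/kg | Gap |
|---|---|---|---|
| 10% | 1 − 0.6 × 0.9 = 46% | 1 − 0.8 × 0.9 = 28% | 18 points |
| 20% | 1 − 0.6 × 0.8 = 52% | 1 − 0.8 × 0.8 = 36% | 16 points |
| 30% | 1 − 0.6 × 0.7 = 58% | 1 − 0.8 × 0.7 = 44% | 14 points |

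The gap is 0.20 × (1 − r), although true reinfection does not differ. At r = 20%, day-21 failures make up 0.40/0.52 = 77% of the positives at 40 mg/kg and 0.20/0.36 = 56% at 60 mg/kg. With 91 per arm, the chance of a significant difference is about 71%, 59% and 47% at r = 10%, 20% and 30%.

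**If some day-21 positives later turn negative**

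Share positive = (1 − c)(1 − k) + c × r, so the gap = 0.20 × (1 − r − k). At r = 20%:
- k = 20%: 0.40 × 0.8 + 0.60 × 0.2 = 44% v 0.20 × 0.8 + 0.80 × 0.2 = 32%, gap 12 points;
- k = 40%: 0.40 × 0.6 + 0.60 × 0.2 = 36% v 0.20 × 0.6 + 0.80 × 0.2 = 28%, gap 8 points.

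This possibility is real. The Introduction reports *S. mansoni* cure at 40 mg/kg of 35%, 56% and 63% at 1, 2 and 6 months.

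**Restricting to day-21 negatives.** In this model both arms then show r and the gap is zero. The denominators are about 0.6 × 91 = 55 and 0.8 × 91 = 73.

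**Effect of section 4.3, if a share f of day-21 failures is re-treated and leaves**

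Share positive = [(1 − c)(1 − f) + c × r] / [(1 − c)(1 − f) + c]. At r = 20%, k = 0:
- f = 0: 52% v 36%, gap 16 points, nobody leaves;
- f = 50%: 0.32/0.80 = 40% v 0.26/0.90 = 29%, gap 11 points;
- f = 100%: 20% v 20%, gap 0. The children leaving number 0.4 × 118 = 47 v 0.2 × 118 = 24, or 36 v 18 of 91.

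The protocol gives no value for f.

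**The case against.** **Section 7.2 does not equate reinfection with one minus the later cure rate.** It says only that the calculations serve to estimate reinfection. Under the model above, the ratio of the two planned cure rates recovers the truth: 1 − 0.48/0.60 = 20% and 1 − 0.64/0.80 = 20%. The individual stool results that any definition needs are collected, and a SAP could supply one. This limits the weight of the point but does not remove it. The ratio appears nowhere in the protocol, while the repeated calculation and its all-subject denominator do. The ratio also fails once some failures turn negative: at r = k = 20% it gives 1 − 0.56/0.60 = 7% and 1 − 0.68/0.80 = 15%.

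**A reader might infer that sections 4.3 and 11 together remove all day-21 failures, about twice as many at 40 mg/kg.** The documents do not support that. The section 11 sentence is followed at once by children who do not qualify for enrolment, and most naturally describes screening and enrolment. No passage re-treats day-21 positives. Section 5.2 lists treatments given after the day-21 assessment without praziquantel, and does not allow anti-schistosomal drugs during the trial. Nor can both harms occur in full: with all failures removed, the spurious reinfection gap vanishes.

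**A reader might also infer that haemoglobin and weight effects are biased toward nil.** No figure in the protocol allows the direction or size to be established. What stands is the rule itself, under which any child who takes such a drug is lost to measurement.

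**The remedy has limits.** Day-21 negatives are themselves a post-randomisation subgroup. Section 12.2 says praziquantel does not act on immature worms, so worms maturing after treatment can look like reinfection. Both limits stand and should be stated with the result.

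**Conclusion.** The reinfection estimate in section 7.2 does not measure reinfection. On the protocol's 60% v 80% cure rates it produces an arm difference of 0.20 × (1 − r), or 18 to 14 points for r between 10% and 30%. This assumes equal true reinfection and failures that stay positive, and the difference shrinks if some day-21 positives later clear.

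The discontinuation rule in section 4.3 is a secondary weakness for haemoglobin and weight at 6 and 12 months, and its size is conditional on a re-treatment practice that the protocol does not state. Losses of up to about 47 v 24 of 118 would arise only if every day-21 failure were re-treated and removed.

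A threat to the main efficacy conclusion should not be read into this. Cure and egg reduction at day 21 are untouched, and later cure, egg reduction and reinfection are not listed endpoints. Severity is moderate to minor.

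**What to change.** - **Section 7.2:** estimate reinfection at 6 and 12 months only among children egg-negative on all day-21 slides, by arm and descriptively. State that this is a post-randomisation subgroup and that worms immature at treatment can mimic reinfection. Report egg-negativity and egg reduction over all randomised children separately, labelled as infection status.
- **Section 4.3:** keep children who take an anti-schistosomal drug in scheduled follow-up, record the drug and date, and analyse haemoglobin and weight as randomised. Add a sensitivity analysis for egg outcomes after re-treatment, without a fixed rule that counts every re-treated child as not cured.
- **Sections 4.3 and 11:** the sponsor must reconcile them on whether the treatment sentence in section 11 applies after enrolment.

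The cost is mainly wording, plus a few recorded items and one sensitivity analysis, since the visits are already scheduled. Keeping re-treated children in the haemoglobin and weight analyses dilutes the dose contrast somewhat, a small price for comparing the arms as randomised. Measurements not taken on discontinued children cannot be recovered later.
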